# Comparing rapid micro-induction and standard induction of buprenorphine/naloxone for treatment of opioid use disorder: protocol for an open-label, parallel-group, superiority, randomized controlled trial

**DOI:** 10.1186/s13722-021-00220-2

**Published:** 2021-02-12

**Keywords:** Micro-induction, Microdosing, Buprenorphine/naloxone, Suboxone, Opioid agonist treatment, Opioid use disorder

## Abstract

**Background:**

Buprenorphine/naloxone (Suboxone) is a current first-line treatment for opioid use disorder (OUD). The standard induction method of buprenorphine/naloxone requires patients to be abstinent from opioids and therefore experience withdrawal symptoms prior to induction, which can be a barrier in starting treatment. Rapid micro-induction (micro-dosing) involves the administration of small, frequent does of buprenorphine/naloxone and removes the need for a period of withdrawal prior to the start of treatment. This study aims to compare the effectiveness and safety of rapid micro-induction versus standard induction of buprenorphine/naloxone in patients with OUD.

**Methods:**

This is a randomized, open-label, two-arm, superiority, controlled trial comparing the safety and effectiveness of rapid micro-induction versus standard induction of buprenorphine/naloxone for the treatment of OUD. A total of 50 participants with OUD will be randomized at one Canadian hospital. The primary outcome is the completion of buprenorphine/naloxone induction with low levels of withdrawal. Secondary outcomes are treatment retention, illicit drug use, self-reported drug use behaviour, craving, pain, physical health, safety, and client satisfaction.

**Discussion:**

This is the first randomized controlled trial to compare the effectiveness and safety of rapid micro-induction versus standard induction of buprenorphine/naloxone. This study will thereby generate evidence for a novel induction method which eliminates substantial barriers to the use of buprenorphine/naloxone in the midst of the ongoing opioid crisis.

*Trial registration* ClinicalTrials.gov, NCT04234191; date of registration: January 21, 2020; https://clinicaltrials.gov/ct2/show/NCT04234191

## Background

The opioid crisis is one of the most serious public health issues in North America in recent years. In the United States, over 45,000 people died from using opioids in 2018, and in Canada, over 17,000 opioid-related deaths have occurred since 2016 [1–4]. Opioid-related deaths have surpassed motor vehicle incidents and homicide deaths combined, resulting in decreases in life expectancy in North America [1, 5].

These deaths are primarily driven by untreated opioid use disorder (OUD), a common disorder affecting millions of individuals worldwide [6]. Current North American guidelines strongly endorse opioid agonist treatment (OAT) with buprenorphine/naloxone as the first-line treatment of OUD, because of its superior safety profile and comparable efficacy over other forms of OAT [7, 8]. OAT is associated with reducing mortality, illicit drug use, and improving physical and mental health outcomes [9].

Buprenorphine is a partial μ-opioid receptor agonist. The partial agonism results in a ceiling effect on respiratory depression and lower risk for overdose [10]. To prevent abuse and minimize diversion, buprenorphine is co-formulated with naloxone, an opioid antagonist, in a 4:1 ratio as buprenorphine/naloxone (brand name: SUBOXONE®) [11]. When buprenorphine/naloxone is injected by individuals with OUD, naloxone precipitates withdrawal. When buprenorphine/naloxone is taken as prescribed, that is sublingually, naloxone is poorly absorbed and does not exert any significant clinical effect, leaving the opioid agonist effects of buprenorphine to predominate.

Buprenorphine exhibits a strong biding affinity to the μ-opioid receptor [10]. When it is introduced in the presence of other opioids with weaker binding affinities, such as heroin, buprenorphine can precipitate withdrawal by displacing other opioids from the receptor. To avoid precipitated withdrawal, the standard method of induction of buprenorphine/naloxone requires patients to be abstinent from other opioids for a set period of time and thus requires patients to be in at least mild withdrawal before its administration [7, 8]. Standard buprenorphine/naloxone induction can thereby be very distressing and time-consuming for patients to tolerate, which can be a barrier for many patients who need this potentially life-saving therapy. Patients who experience precipitated withdrawal or significant levels of withdrawal during the induction process may also be less likely to be retained in treatment [12].

To overcome the difficulties of a standard induction method of buprenorphine, a novel induction method, known as micro-induction (also called micro-dosing), is being explored and increasingly employed by many clinicians in Canada, the United States, and other parts of the world [13–21]. This induction method was first described as the Bernese method in a Swiss case series in 2016 [14]. The method involves administering buprenorphine at micro-doses once to twice daily, concurrently with the use of a full μ-opioid receptor agonist, to avoid precipitated withdrawal. It did not require the two outpatients to go through withdrawal from opioids prior to induction, and they reached therapeutic doses in 10 or more days.

Recently, our team developed a more rapid variation of micro-induction, known as rapid micro-induction, which was developed to be primarily used in an inpatient setting. It involves the administration of buprenorphine/naloxone every 3 to 4 h along with the use of a full μ-opioid receptor agonist, resulting in patients reaching therapeutic doses in just three to five days [17]. The rationale of this rapid dosing is based on the hypothesis that buprenorphine reaches peak plasma concentration in approximately an hour [22]. Rapid micro-induction offers several advantages over a standard induction method—eliminating the abstinence period preceding induction, reducing the risk of precipitated withdrawal, minimizing the symptoms of withdrawal and craving, potentially improving treatment retention, and reducing the time spent in hospital [17, 19].

Rapid micro-induction and variations of this novel induction method have been extensively described in several case reports and in a recent review, however, they have never been systematically evaluated in a clinical trial [13–21]. To generate the evidence for this induction method in the midst of the ongoing opioid crisis, the first randomized controlled trial was developed to compare the effectiveness and safety of rapid micro-induction versus standard induction of buprenorphine/naloxone.

## Study design

### Overview of study design

This study is a randomized controlled trial comparing the effectiveness and safety of rapid micro-induction versus standard induction of buprenorphine/naloxone. It has received approval from the Research Ethics Board of the University of British Columbia (H19-03254) and is registered in clinicaltrials.gov (NCT04234191). In this open-label superiority trial, eligible patients with OUD will be randomized to either: (a) the rapid micro-induction arm or (b) the standard induction arm (treatment as usual).

The study schema is presented in Fig. 1. The study will take place at one site, Vancouver General Hospital (VGH) in Vancouver, British Columbia, Canada. The Complex Pain and Addiction Services (CPAS) is a consulting service in which VGH inpatients with substance use disorders are referred to for treatment and counselling. The study staff at CPAS will pre-screen referrals to determine general eligibility for participation in the study. Patients will then be invited by the study staff to complete the informed consent procedures. Once informed consent is provided, participants will undergo screening procedures to confirm their eligibility.

**Fig. 1 Fig1:**
[figure not shown]
Study schema

Eligible participants will be randomized on an allocation ratio of 1:1 to either of the two arms, using a blocked permuted block design with block sizes of 4 and 6. Randomization will be managed with the REDCap platform [23, 24]. Once randomized, participants will complete baseline assessments and be followed for 7 days. Towards the end of the intervention period, the physician in charge will inform all participants about follow-up treatments that are available to them. Participants will receive follow-up with their community addictions physicians and/or the CPAS outpatient clinic.

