## Outcomes and assessments

The timeline of assessments is shown in Table 3. It should be noted that there is an additional day of assessments conducted with the experimental arm, because the experimental intervention (rapid micro-induction) takes one day longer than the treatment-as-usual intervention (standard induction).

**Table 3 Tab3:** Timeline of assessments

Assessments	Screening	Randomization	Baseline^d^	Day 1^d^	Day 2	Day 3	Day 4	Day 7
Experimental arm: rapid micro-induction (E stands for experimental arm assessments)								
Control arm: standard induction (C stands for control arm assessments)								
Informed consent form	E C							
Physical examination	E C		E C	E C	E C	E C	E	
Medical history	E C							
Pregnancy test	E C							
Blood tests^a^	E C							
Viral profile^b^	E C							
Urine drug screens	E C		E C		C	E		
Opiate treatment index (OTI)—health section			E C					
Treatment outcomes profile (TOP)			E C		C	E		
Clinical Opiate Withdrawal Scale (COWS)			E^c^ C^c^	E^c^ C^c^	E^c^			
Numeric Rating Scale for craving			E^c^ C^c^	E^c^ C^c^	E^c^			
Numeric Rating Scale for pain			E^c^ C^c^	E^c^ C^c^	E^c^			
Treatment Perceptions Questionnaire (TPQ)					C	E		
Assessment of treatment retention								E C
Adverse event report form			E C	E C	E C	E C	E	

^a^Complete blood count (CBC), Extended lytes, Liver function

^b^HepC serology, HepB antigen, HIV Elisa

^c^The COWS and Numeric Rating Scales for craving and pain will be administered at baseline, every 1.5 h during the abstinence period (control arm only), and throughout the induction process for both arms (days 1 to 2 of the experimental arm, and day 1 of the control arm)—specifically, immediately before each dose of buprenorphine/naloxone, and 1 to 1.5 h after each dose of buprenorphine/naloxone

^d^Baseline and day 1 assessments may be done on the same day, depending on the time of day the participants are recruited in the study and the state they are in when they are recruited

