### Primary outcome

The primary outcome is the completion of buprenorphine/naloxone with low levels of withdrawal. Success on the primary outcome is defined as the following: participants who remain in treatment until they have received a total dose of ≥ 8 mg of buprenorphine/naloxone within a 24-h period (successful induction), and score ≤ 12 on the COWS (low levels of withdrawal) from baseline to when they reach that dose [29]. The COWS will be administered at baseline, every 1.5 h during the abstinence period (control arm only), and throughout the induction process for both arms (days 1 to 2 of the experimental arm, and day 1 of the control arm)—specifically, immediately before each dose of buprenorphine/naloxone, and 1 to 1.5 h after each dose of buprenorphine/naloxone. Our primary hypothesis is that there will be a significantly higher number of participants in the rapid micro-induction arm who will be successfully induced onto buprenorphine/naloxone with low levels of withdrawal, compared to participants in the standard induction arm.

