### Primary outcome

The primary outcome will be assessed in a binary fashion: participants need to fulfill both criteria (successful induction and low levels of withdrawal) in order to be successful with the primary outcome. Outlier COWS scores will be checked and confirmed with the clinical records on an ongoing basis by the study coordinator. Effort will be made by the study team to avoid missing COWS scores during the study. In case of missing scores, multiple imputation will be used to impute the missing variables, and sensitivity analysis will be performed by once assigning failure to all the missing COWS score and then success to them, then describing and explaining the impact on the results. Fisher’s exact test will be used to compare two groups with a significance level set at 0.05. To demonstrate the effect size, we will use both unadjusted and adjusted odds ratios with 95% confidence intervals using logistic regression. In the latter, effect size will be adjusted for age, gender, and baseline COWS score in addition to allocated arm. Adjustment for baseline covariates will improve the sensitivity of the comparison.

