We believe that the findings from this study will be generalizable to clinical settings in many jurisdictions, including settings with patients who use fentanyl. In British Columbia, there has been a surge in fentanyl-detected overdose deaths, as fentanyl was only detected in 5% of illicit drug deaths in 2012 but was detected in 87% of the deaths in 2019 [35]. Deaths involving fentanyl have also rapidly increased across many states in the United States [36, 37]. Furthermore, buprenorphine for the treatment of OUD has become increasingly available in the United States [25]. A limitation in our study is the administration of hydromorphone during the first 2 days of the rapid micro-induction arm, as some jurisdictions may face regulatory barriers when using hydromorphone with the induction method. However, it should be noted that in the context of the study, hydromorphone is used on an as-needed basis to meet the patient’s opioid requirements during the induction process. In clinical practice, we use the rapid micro-induction method with any opioid based on the patient’s preferences and clinical indications. We plan to conduct future studies where patients on methadone are not excluded and other opioids are used instead of hydromorphone.

The open-label design of this clinical trial may also introduce the risk of potential bias. However, it is not feasible to blind participants or researchers due to the nature of the interventions. The study may also benefit from a large sample size and a longer duration of follow-up, but such changes are not possible due to resource and cost constraints. Despite these limitations, the evaluation of the primary and secondary outcomes will greatly contribute to our understanding of rapid micro-induction. As the opioid crisis in North America continues, the results derived from this clinical trial will generate the first major body of clinical evidence on the effectiveness and safety of rapid micro-induction, a novel and patient-centered induction approach which could immensely improve the accessibility of buprenorphine/naloxone for patients with OUD.

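### Baseline COWS is taken after open-label randomisation, yet it counts in the primary outcome and is its adjustment covariate, which leaves the comparison open to avoidable bias

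*Protocol article*

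**What the plan says.** The order of events is in the overview of the study design: "Once randomized, participants will complete baseline assessments and be followed for 7 days". Table 3 agrees. Its Randomization column comes before its Baseline column, and the first COWS, craving and pain ratings are at Baseline, with none at Screening. The Discussion accepts that "it is not feasible to blind participants or researchers due to the nature of the interventions".

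The baseline COWS then has two uses.

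- **Endpoint.** Under Outcomes and assessments, Primary outcome, success needs a score of 12 or less "on the COWS (low levels of withdrawal) from baseline to when they reach that dose". The same paragraph says "The COWS will be administered at baseline", so that score is the first in the window. The eligibility criteria set no COWS limit.
- **Covariate.** Under Data analysis, Primary outcome, "effect size will be adjusted for age, gender, and baseline COWS score in addition to allocated arm".

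The primary comparison itself is unadjusted: Fisher's "exact test will be used to compare two groups with a significance level set at 0.05". The unadjusted and adjusted odds ratios describe effect size.

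**The concern.** A baseline covariate is safe to adjust for because allocation cannot have affected it. Here the participant and the rater can both know the arm when the score is taken. Two routes are open: the rating may lean one way because the arm is known, or the participant's state may change while waiting after allocation. If either happens differently by arm, the adjusted odds ratio conditions on something that allocation has altered.

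Because the score is also part of the endpoint, the unadjusted Fisher test is not fully protected. A difference between arms in the share scoring 13 or more at baseline feeds straight into the failure rate. Baseline craving and pain are self-reported at the same moment, and the repeated-measures interaction terms use them.

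No later analysis can recover a pre-allocation COWS that was never recorded, so this is not a detail that a statistical analysis plan could settle.

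**Working it through.** **1. The plan's own figures.** Inputs from the sample size section: success 95% vs 10%, type I error 0.05, power 0.90, Fisher's exact test. Full enumeration of two binomials gives power 0.945 at 6 per arm one-sided, which reproduces the stated 12. Two-sided power is 0.774 at 6 per arm and 0.919 at 7. Attrition: 12 / 0.9 = 13.3, so 14, as stated. At the target of 25 per arm, two-sided power exceeds 0.9999. The point is therefore about bias and interpretation, not about numbers enrolled.

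**2. Automatic failures, equal in both arms.** Let q be the share with baseline COWS of 13 or more. The documents give no value, so q is assumed. The success rate becomes planned rate × (1 − q), with 25 per arm:

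| q | Expected failures among 50 | Experimental | Control | Two-sided Fisher power |
|---|---|---|---|---|
| 5% | 2.5 | 0.95 × 0.95 = 90.25% | 9.5% | >0.999 |
| 10% | 5 | 0.95 × 0.90 = 85.5% | 9.0% | >0.999 |
| 20% | 10 | 76% | 8% | 0.9997 |
| 40% | 20 | 57% | 6% | 0.979 |

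The difference shrinks, from 85 points to 76.5 at q = 10%, but neither arm is favoured and power holds.

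**3. Automatic failures, unequal between arms, with no effect after baseline.** Success in each arm = p × (1 − q), with the same p in both. Rejection rate of the two-sided 0.05 Fisher test, 25 per arm, all shares assumed:

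| q experimental vs control | p = 0.95 | p = 0.50 |
|---|---|---|
| 10% vs 10% | 1.8% | 3.2% |
| 10% vs 20% | 7.4% | 4.2% |
| 10% vs 30% | 23% | 7.4% |
| 10% vs 40% | 49% | 13.5% |

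The primary test is disturbed only if the shares differ materially by arm.

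**4. The adjusted odds ratio.** Large-sample simulation (400,000 subjects). Assumptions: underlying COWS mean 8, SD 3; baseline measurement error SD 1; later score = state at baseline + 1 with error SD 2; success if baseline and later scores are both 12 or less. Odds ratios above 1 favour the experimental arm.

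| Scenario | Unadjusted | Adjusted for post-randomisation baseline |
|---|---|---|
| No effect, no shift | 1.00 | 1.00 |
| Effect of 3 points, no shift | 2.29 | 6.31 |
| No effect, control baseline rated 2 points higher | 1.58 | 0.28 |
| No effect after baseline, control truly 2 points higher after waiting | 2.73 | 1.19 |

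What this shows:

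- With no shift by arm, adjusting for the post-randomisation score gives 6.31 and adjusting for the pre-randomisation score gives 6.40. Timing alone does essentially no harm.
- With a pure rating shift, the two odds ratios fall on opposite sides of 1. On the log scale the adjusted one moves further: ln 0.28 = −1.27 against ln 1.58 = 0.46.
- If the experimental arm were rated 2 points higher instead, relabelling the arms gives 1/1.58 = 0.63 and 1/0.28 = 3.6. The direction is not fixed.
- With a real rise from waiting, adjustment removes most of the difference that the unadjusted figure carries, so the two odds ratios answer different questions.
- In the rating-shift row, adjusting for a pre-randomisation score while the shifted baseline still counts in the endpoint gives 3.07. An extra screening COWS used only as covariate would not be enough; the baseline measurement itself has to move.

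**The case against.** The strongest reply is that nothing in the article shows allocation changing the score. A reader might infer that control baselines already contain abstinence, and experimental ones hydromorphone. The documents point the other way. The Primary outcome section and footnote c of Table 3 list the baseline COWS separately from the control arm's abstinence ratings, and Table 1 starts hydromorphone on day 1, after the Baseline column. Footnote d says "Baseline and day 1 assessments may be done on the same day", which permits the same day but does not place baseline after either step. The state of participants at recruitment, which that footnote mentions, precedes allocation and is balanced in expectation. This reply stands against any claim that the adjusted effect is biased. It leaves unblinded rating and delay after allocation as possible routes.

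Three other strong readings also fail.

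- **The main result is compromised.** The primary test is an unadjusted Fisher test and the adjusted odds ratio is supportive, so the exposure of the main inference is smaller.
- **Automatic failures worsen separation in the logistic model.** For the arm term they do the opposite. The chance of an all-success experimental arm or a no-success control arm is 1 − (1 − 0.95^25)(1 − 0.90^25) = about 33% as planned. With 10% automatic failures it is 1 − (1 − 0.855^25)(1 − 0.91^25) = about 11%.
- **The baseline score should simply be dropped from the endpoint.** COWS is also taken immediately before each dose, including the first, so a participant who stays at 13 or more would fail anyway. Counting withdrawal from the start also fits an endpoint meant to capture withdrawal before dosing.

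**Conclusion.** The point holds in limited form: the stated order leaves the adjusted odds ratio open to bias and, to a lesser extent, the Fisher comparison and the secondary analyses that depend on baseline. Size and direction are unknown. The figures above rest on assumed COWS distributions, shifts and shares; they show how the mechanism works and do not estimate what will happen in this trial.

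A participant with a baseline COWS of 13 or more can fail before any study dose in either arm. The documents give no frequency, and they do not say whether the expected 95% success already allows for such failures. If the share is equal in both arms, the difference is diluted and neither arm gains.

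This is a cheap improvement that should be made; it does not invalidate the trial.

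**What to change.** - Complete all baseline assessments after eligibility is confirmed and before the REDCap allocation is revealed. Re-order the sentence in the study design overview and the columns of Table 3 to match.
- Use that pre-randomisation COWS as the covariate in the adjusted model.
- State in the primary outcome definition whether a baseline score above 12 counts as failure.

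The cost is the re-ordering of one visit, with the same staff and forms, and short text edits. The article describes the site as still preparing for recruitment. The downside is that a few participants may be assessed and then not randomised. Re-timing does not blind the later COWS ratings; that limitation of the open-label design remains.

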### Study objectives

The primary objective is to compare rapid micro-induction versus standard induction on the successful induction of buprenorphine/naloxone with low levels of withdrawal in patients with OUD. The secondary objectives are to evaluate treatment retention, illicit drug use, self-reported drug use behaviour, craving, pain, physical health, safety, and client satisfaction.

